#### Nurse practitioners-related

For NPs, we will record g*ender*, *age*, *educational level*, *years of experience as nurse practitioner*, *institute* and *department*.

### Intervention fidelity

The effect of the intervention will depend on adherence to the intervention protocol. The risk of not assessing the intervention fidelity is that it might be difficult to find out whether (non)significant findings are caused by how the intervention was administered or by the intervention itself [47]. Therefore, for each patient that receives the intervention, the NP will complete a questionnaire focusing on intervention fidelity. In this questionnaire, NP will be asked to answer questions about the number of consultations the patient received, how often the Self-Management web was used and if every step of the intervention was completed.

### Evaluation of experience

Participating patients will be asked about their experience with and the amount of nurse-led care on medical, emotional and social aspects, using questions included in the post-intervention measurement (T1). Overall experience of the nurse-led care will be assessed using a visual analogue scale and the Dutch translation of the subscale ‘patient-centeredness’ of the American Consumer Assessment of Health Plan Survey (CAHPS) [48]. We will use five questions of the subscale (Cronbach’s *α* = .83) [31].

Answer options for the three separate questions on the amount of the nurse-led care on medical, emotional and social aspects will be (0) ‘very little’ to (4) ‘very much’. Patients in the experimental period will also be asked about the experience with the intervention using open questions for experience with the intervention.

All participating NPs will be interviewed at the end of the experimental period about possible obstacles to implementation, room for improvement, advice for further development and implementation in clinical practice.

### Sample size

The sample size calculation is based on a power calculation for the primary outcome i.e. the Skills and Technique acquisition scale of the heiQ at T1. Previous studies have shown effect sizes (Cohen’s *d*) of similar interventions on the Skills and Technique Acquisition scale of 0.17, 0.50, 0.25, 0.50, 0.31 and 0.59 [49–54]. Based on these previous results, we estimate the effect size of the intervention to be 0.38, which is the average effect size observed in the previous studies. Using an ANCOVA model applied at the patient level, with an adjustment for baseline Skills and Technique Acquisition and treatment group (pre- or post-intervention), 82 patients per group are needed to obtain a power of 80% to detect a significant effect of the intervention, at a two-sided significance level of .05. To account for the effects of adjustment for covariates, dropout and missing data, and contamination, we aim to include 100 patients per group, 200 in total. Note that the ANCOVA model assumed in the power analysis differ slightly from the linear mixed model described for the primary analysis below.

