## Methods/design

### Study design and randomization

This multi-centre study in the Netherlands has an unblinded stepped wedge cluster randomized design [32] with pre- (T0) and post-intervention measures after six months (T1), with a follow up after twelve months (T2). The framework of this trial is superiority, whereby we will compare the outcomes between the control and intervention group, and between baseline and follow up data. Seven departments of five University Medical Centres will participate in the study, four kidney transplantation units, one heart transplantation unit, one liver transplantation unit and one lung transplantation unit. The coordinating centre is Erasmus MC, department Nephrology and Transplantation. This department is responsible for coordinating the study, distributing the questionnaires, training of the NPs and the data analysis. A steering committee is present to contribute ideas and to oversee the process.

Given the nature of the programme and the fact that NPs are trained in delivery of the intervention and communication skills, the NPs delivering the intervention cannot be blinded to the group allocation. Therefore, randomization will be performed at the department level. This will be carried out by an independent professional not involved in the study using sealed opaque envelopes. The envelopes with department names and envelopes with start date will be prepared and shuffled by the researcher. The independent professional then randomly chooses the envelopes. All seven participating departments commence the study with standard care i.e. the control period (see Fig. 1) in September 2020. The timing of transition of departments from control to experimental  period is randomized. The first department will be randomized to commence the experimental period in March 2021. During the experimental period, patients receive standard care plus the ZENN intervention. Patients in the control period are different from the experimental period patients, meaning that they will not cross-over.

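### The 80% power with 82 per group is that of an individually randomised ANCOVA; once calendar time is adjusted for, this seven-department stepped wedge has far less

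*Protocol article*

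**What the plan says.** All of the following is in the protocol article.

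- Sample size: the effect size is the mean of six earlier results ("we estimate the effect size of the intervention to be 0.38, which is the average effect size observed in the previous studies"). The model is given as "Using an ANCOVA model applied at the patient level, with an adjustment for baseline Skills and Technique Acquisition and treatment group", and the result is that "82 patients per group are needed to obtain a power of 80% to detect a significant effect of the intervention". The test is two-sided at 0.05.
- Sample size, on the margin: the target is raised to 100 per group (200 overall) to cover covariate adjustment, dropout, missing data and contamination. Clustering by department and calendar time are not among the reasons.
- Sample size, closing remark: "Note that the ANCOVA model assumed in the power analysis differ slightly from the linear mixed model described for the primary analysis below".
- Study design and randomization: "Seven departments of five University Medical Centres will participate in the study". Departments are the randomised units. All start in the control condition in September 2020, the first crosses in March 2021, and control and experimental patients are different people.
- Data analysis: the mixed model is to account for repeated measures, organ, transplant centre and other significant covariates. No calendar-period term is named. T0, T1 and T2 measure time since a patient's own baseline, not calendar time.
- Trial status: inclusion is expected to end in May 2022.

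**The concern.** In a stepped wedge, experimental patients are on average recruited later than control patients. Here recruitment runs through a pandemic that, by the article's own account, might move delivery to tele-medicine. Separating the intervention from time means estimating calendar-period effects, and this inflates the variance of the treatment effect even when departments do not differ at all. A patient-level ANCOVA with only baseline score and group carries none of that cost, nor any department effect.

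The 80% is what a reader will use to interpret a null result. If the analysis that isolates the intervention has about half that power at the assumed effect, a null result would be read as stronger evidence against the intervention than it is.

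**Working it through.** **1. Reproducing 82.** Inputs from the Sample size section: d = 0.38, two-sided 0.05, power 80%. (The six listed values average 2.32/6 = 0.387.)

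- Without baseline adjustment: 2(1.96 + 0.842)^2 / 0.38^2 = 108.7, so 109 per group (110 by exact t).
- ANCOVA multiplies this by 1 - r^2. With r = 0.5, 108.7 x 0.75 = 81.5, so 82.
- Power is 0.80 with 82 per group and 0.87 with 100 per group.

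The article does not give r; 82 implies about 0.50. No cluster or period term is needed to reach it.

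**2. Set-up for the stepped wedge.** Taken from the article: seven departments, a six-month control lead-in (September 2020 to March 2021), recruitment to May 2022 (taken as 20 months) and different patients in the two conditions. Carried over from step 1: d = 0.38 and residual variance 0.75. Assumed: one department crosses per step, steps of 2 or 1.5 months, equal departments, uniform recruitment, ICC 0 to 0.05, normal approximation.

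**3. Cost of period adjustment alone (ICC 0).** Let w_j be the share of patients recruited in period j and q_j the fraction of departments already crossed. The variance relative to a balanced two-arm trial is

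DE = 0.25 / sum of w_j q_j (1 - q_j).

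The lead-in (q = 0) and the last period (q = 1) contribute nothing. For the six middle periods, the sum of q(1 - q) is (6 + 10 + 12 + 12 + 10 + 6)/49 = 1.143.

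- 2-month steps: w = 2/20, so DE = 0.25 / 0.1143 = 2.19.
- 1.5-month steps: w = 1.5/20, so DE = 0.25 / 0.0857 = 2.92.

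SE = sqrt(DE x 4 x 0.75 / N), and power = Phi(0.38/SE - 1.96). For 2-month steps and N = 164, SE = sqrt(2.19 x 3/164) = 0.200 and power = Phi(1.90 - 1.96) = 48%.

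**4. Adding departments.** Generalised least squares with period effects and a random department effect (Hussey-Hughes model), or with fixed department effects:

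| Steps | Departments | Power, 164 analysed | Power, 200 analysed |
|---|---|---|---|
| 2 months | random, ICC 0 | 48% | 56% |
| 2 months | random, ICC 0.05 | 42% | 48% |
| 1.5 months | random, ICC 0 | 38% | 44% |
| 1.5 months | random, ICC 0.05 | 34% | 40% |
| 2 months | fixed | 33% | 39% |
| 1.5 months | fixed | 29% | 34% |

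With 2-month steps and 164 patients, period adjustment takes power from 80% to 48%; an ICC of 0.05 takes it on to 42%. Steps of one month, with recruitment to the end of May 2022, give about 22-30% (random or fixed departments, 164 or 200 analysed).

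**5. Detectable effect at 80% power, N = 200, ICC 0.05.** 2.80 x sqrt(DE x 4 x 0.75/200). DE = 2.63 (2-month steps) gives 0.56 SD; DE = 3.29 (1.5-month steps) gives 0.62 SD.

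**6. The same schedules without period terms.**

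- Random departments, ICC 0: DE = 0.25 / [p(1 - p)], with p the overall control share. For p = 0.60 (2-month steps) it is 1.04, and for p = 0.525 (1.5-month steps) it is 1.00.
- Fixed departments: the denominator is the mean of p(1 - p) within departments. With 2-month steps the control shares are 0.3, 0.4, ..., 0.9, the mean is 0.20, and DE = 1.25. With 1.5-month steps they are 0.3, 0.375, ..., 0.75, the mean is 0.227, and DE = 1.10.

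Power then lies at about 71-80% with 164 analysed and 79-87% with 200.

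**The case against.** The strongest reply is that the Data analysis section lists no calendar-period term. For the terms it does list, step 6 shows that the stated 80% is roughly right. That stands. A reader might infer that the trial as planned simply delivers half its stated power; the article does not support this without the condition that period is modelled. The reply does not rescue the power claim, though. Without period terms the comparison mixes the intervention with whatever changed between September 2020 and May 2022.

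Four further points are fair.

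- The figure of 82 is not an arithmetic slip. It reproduces, and the article says openly that it rests on a patient-level ANCOVA and that the analysis model differs.
- The step dates cannot be called missing. The text refers to Fig. 1, which is not reproduced in the copy at hand and may show them. A fuller analysis plan might also add period terms.
- A reader might take eight equal periods as the natural default, which gives a design effect of 1.75 and 65% power with 200 patients at ICC 0. Over 20 months that puts the first crossing at month 2.5, which the March 2021 date rules out.
- The mixed model also uses T2, which may recover a little precision. But the sample size is stated for T1, and T2 does not separate treatment from calendar time.

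**Conclusion.** The concern holds in conditional form. The 80% belongs to an individually randomised comparison with a baseline correlation of about 0.5. In this stepped wedge, an analysis that separates the intervention from calendar time has, at d = 0.38, about 34-48% power with 164 analysed and 40-56% with 200 (random departments), or 29-33% and 34-39% (fixed departments). The 164 figures are the closer guide, because the other 36 patients are already allotted to dropout, missing data, covariates and contamination.

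The percentages rest on assumed step spacing, ICC, equal departments and uniform recruitment. Shorter steps lower them, and the normal approximation is optimistic with seven clusters. No period-adjusted scenario examined comes near 80%. The remark that the two models differ only slightly does not hold once period is fitted.

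**What to change.** Keep the sample size and replace the power statement with one for the design as randomised:

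- seven departments, the real step schedule and calendar period in the model;
- a range of ICCs, for example 0, 0.02, 0.05 and 0.10;
- the assumed baseline correlation and the number expected to be analysable;
- the resulting power at d = 0.38, and the effect detectable with 80% power (about 0.56-0.62 SD at ICC 0.05 and 200 analysed under the steps assumed here).

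Say which analysis the figure covers. This needs stating because the Sample size section treats the mixed model as primary, while the Data analysis section gives that label to a univariate comparison. Delete the remark that the models differ slightly.

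The cost is one rewritten paragraph and a less favourable stated power. Recruitment and conduct are unchanged.

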### Data analysis

Data will be coded with a unique code per patient. The key of these codes will be safeguarded by the coordinating and the principal investigator with a password. No other persons will have access to the key. All data will be kept for 15 years, according to the Dutch Personal Data Protection law. Data will be stored using the data capture applications Gemstracker and Limesurvey. These systems are managed by the Department of Information Management of Erasmus MC and are secured with an individual password for the coordinating and principal investigator.

To assess if randomization has resulted in comparable groups, we will compare patients in the control and in the experimental period at baseline (T0) on characteristics as well as primary and secondary outcomes. Descriptive statistics will be presented as frequencies (%) for categorical variables. Continuous variables will be described as median and interquartile range for non-normally distributed variables and as mean and standard deviation for normally distributed data.

The primary analysis of the study is an initial univariate exploration of the effect of the intervention. Continuous outcomes at T1 between the patients in the control and experimental period will be compared and tested using the Mann-Whitney *U* test for non-normally distributed data and the independent-samples *t* test for normally distributed data. For the BAASIS, a 2 × 2 chi-squared test will be conducted (adherent yes/no × control/experimental group). In univariate analyses, the relationship between patient characteristics (such as age and gender) and medical characteristics (such as organ type and centre) and the outcomes will be assessed.

For the multivariate analyses, linear mixed models analysis will be conducted to account for repeated measures per patient, covariates organ and transplant centre and other significant covariates. All models will be estimated using intention-to-treat analysis incorporating all eligible patients from whom data was obtained. There are three measurement time points (T0, T1 and T2) to be included in these analyses. For missing data in predictor variables, we will use multiple imputation. A *p* value < 0.05 is considered statistically significant.

We will assess the differences on the primary and secondary outcomes between patients in the control period and versus the experimental period at both T1 and T2 on the outcomes (between-groups comparison). We will also assess the differences on the outcomes between T0–T1 and T0–T2 within the control period and within the experimental period (within-groups comparison). The secondary outcome measure *medication adherence*, which is a dichotomous variable, will be analysed with a generalized estimating equations logistic regression. If the effect of the intervention is found to differ according to organ type then separate explorative multivariate analyses will be conducted to assess the effect per organ.

Among NPs, in an initial univariate analysis, we will compare self-management support skills, using all scales of the SEPSS-36, before and after the experimental period (T0-prior to training and T1-at the end of the implementation period). For non-normally distributed data, we will use the Wilcoxon signed-rank test and the paired samples *t* test in case of normally distributed data.

The video recordings of the NPs will be assessed in blocks of 5 minutes each. Of every recording, a 5-minute clip will be randomly assigned to be observed by two researchers independently. The clips from the control period will be compared with the clips of the experimental period on the needs-thwarting and needs-supporting subscales and tested using the Wilcoxon-signed rank test for non-normally distributed data and the paired samples t-test in case of normally distributed data.

The interviews and qualitative questions in the questionnaire, which will be used to qualitatively evaluate the intervention and the nurse-led care, will be transcribed by at least two researchers independently and analysed thematically [55] using NVivo.

To examine if contamination occurred, we will compare the primary outcome (Skills and Technique Acquisition - heiQ) among control period patients in the contamination phase versus those in the control period not in the contamination phase at T1 and T2. This will be done using an independent samples *t* test. If there is a significant difference, we will control for contamination in the main multivariate analysis.

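### The protocol article names two different primary analyses, and the one it declares in Data analysis (an unadjusted T1 test) omits baseline, department and calendar time and falls short of the stated 80% power

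*Protocol article*

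**What the plan says.** All references are to the protocol article.

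- Data analysis, on what is primary: "The primary analysis of the study is an initial univariate exploration of the effect of the intervention". The method follows: "Continuous outcomes at T1 between the patients in the control and experimental period will be compared and tested using the Mann-Whitney" test or, for normally distributed data, the independent-samples t test.
- Sample size, on what is primary: "Note that the ANCOVA model assumed in the power analysis differ slightly from the linear mixed model described for the primary analysis below". The power calculation itself uses a patient-level ANCOVA adjusted for the baseline score, with d = 0.38, two-sided alpha 0.05, 82 patients per group for 80% power, and 100 per group to be included.
- Data analysis, on the mixed model, introduced as a multivariate analysis and not called primary: "linear mixed models analysis will be conducted to account for repeated measures per patient, covariates organ and transplant centre and other significant covariates". T0, T1 and T2 all enter it.
- Data analysis, on contamination: "we will control for contamination in the main multivariate analysis".
- Study design and randomization: "Therefore, randomization will be performed at the department level". "Seven departments of five University Medical Centres will participate in the study". All start in the control period in September 2020. "The first department will be randomized to commence the experimental period in March 2021". Control and experimental patients are different people.

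**The concern.** The article gives the primary label to one analysis in one section and to another in the next, for the same outcome. If the two disagree, nothing says which result answers the trial's question, and the choice could be made after the data are seen. This is a conflict between statements already made, not detail left for a fuller document.

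Read literally, the declared test does not fit the design. It treats patients as if they had been randomised individually, discards the T0 score that the power calculation relies on, and compares patients included later with patients included earlier. In a stepped wedge that last feature is built in, so any change over calendar time is mixed with the intervention effect. The article notes that COVID-19 might move both the training and the intervention to remote delivery, so stable conditions from September 2020 onwards cannot be taken for granted.

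**Working it through.** **1. Reproducing the plan's 82 per group.** Inputs from Sample size: d = 0.38, two-sided alpha 0.05, power 80%. The correlation r between T0 and T1 is not given.

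n per group = 2 × (1.960 + 0.842)² / d² × (1 − r²) = 2 × 7.849 / 0.1444 × (1 − r²) = 108.7 × (1 − r²)

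- r = 0.5: 81.5, so 82. This matches the plan.
- r = 0.3: 99; r = 0.4: 92; r = 0.6: 70.
- r = 0 (no baseline adjustment): 109, or 110 with the exact t test.

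So 82 belongs to a baseline-adjusted analysis with r of about 0.5.

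**2. Power of the test declared primary.** Noncentral t with noncentrality d × √(n/2), independent patients, no dropout:

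- n = 82: 0.38 × √41 = 2.43, power 67.7%.
- n = 100: 0.38 × √50 = 2.69, power 76.2%.
- Mann-Whitney with normal data (n multiplied by 0.955): about 66% and 74%.
- For comparison, ANCOVA with the assumed r = 0.5: about 80% and 87%, ignoring clustering and period.

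The unadjusted figures need no assumed correlation.

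**3. Ignoring department (illustrative).** The article text gives no ICC, and the inclusion figure is not available to this review. Assumptions: seven equal departments, 200 patients, uniform inclusion over 20 months (September 2020 to May 2022, Trial status), first crossover at month 6.

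Variance ratio = [ICC × Σw² + (1 − ICC) × (1/Nc + 1/Ne)] / (1/Nc + 1/Ne), where w is a department's share of experimental patients minus its share of control patients.

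Example with crossovers evenly spaced over months 6–16: Ne = 90, Nc = 110, Σw² = 0.0648, 1/Nc + 1/Ne = 0.0202. At ICC 0.05 the ratio is 1 + 0.05 × (0.0648/0.0202 − 1) = 1.11, and the type I error is 2 × [1 − Φ(1.96/√1.11)] = 6.3%.

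| Crossovers | ICC 0.01 | ICC 0.05 | ICC 0.10 |
|---|---|---|---|
| monthly, months 6–12 | 5.0% | 5.1% | 5.2% |
| even, months 6–16 | 5.3% | 6.3% | 7.6% |
| even, months 6–18 | 5.4% | 7.2% | 9.5% |

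**4. Ignoring calendar time (illustrative).** With crossovers over months 6–16, experimental patients enter on average about 8.9 months later, 0.44 of the window. A trend of 0.2 SD over inclusion then gives a spurious difference of 0.44 × 0.2 = 0.09 SD; 0.4 SD gives 0.18 SD. Simulated type I error of the unadjusted t test (8000 replicates, ICC 0 to 0.10) is 9–13% and 23–27% respectively.

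**5. What a model that fits the design would cost (illustrative, r = 0.5, same layout).** Power = Φ(0.38/SE − 1.96), with SE² = V × 2 × 0.75/100 = 0.015 × V. V is 0.25 divided by the mean squared residual of the treatment indicator after regression on the other design terms.

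- Department only: V = 1.05 to 1.25, power about 86% to 79%.
- Department and calendar month, crossovers monthly in months 6–12: V = 5.3, SE = 0.282, power Φ(1.348 − 1.96) = 27%.
- Department and a linear time trend, crossovers over months 6–18: V = 3.1, SE = 0.216, power Φ(1.762 − 1.96) = 42%.

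The department term costs little; the time term costs most of the stated power.

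**The case against.** The strongest reply is that the mixed model was meant all along. The sentence in Data analysis speaks of an initial exploration, similar words describe a preliminary step for the nurse practitioners, the sample-size note names the mixed model, the contamination paragraph treats the multivariate analysis as the main one, and the first aim in the Introduction is stated with control for patient characteristics. This is persuasive about intent. A reader might infer that the trial will rest on the t test; the documents do not establish that. The conflict remains, because the only sentence that defines the primary analysis points to the unadjusted test.

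A reader might also infer that the mixed model ignores the randomised unit. That is not supported. It uses T0 and adjusts for organ and centre. Heart, liver and lung have one unit each, so organ identifies them. Centre separates the four kidney units if they lie in different centres. Together the two terms probably identify the department.

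Nor can the missing period term count only against the unadjusted test: the mixed model as described names none either.

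Finally, a reader might infer a clearly inflated false-positive rate. Clustering alone may leave it close to 5%, as the first column and first row of the table show. The larger values depend on an ICC, a step schedule or a time trend that the article does not give.

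**Conclusion.** The contradiction holds: one outcome, two analyses labelled primary, no rule between them. It should be settled before analysis because it decides which p-value answers the trial's question.

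The firm part of its size is the power. At d = 0.38 the declared test has about 68% with 82 per group and 76% with 100, against the stated 80%, before any clustering or dropout. It would need 110 per group. That 82 rests on baseline adjustment follows from the formula; the value r = 0.5 is an inference from it.

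The type I figures are illustrative. Without a time trend they are about 5% at ICC 0.01, 5–7% at ICC 0.05 and 5–9.5% at ICC 0.10, depending on the assumed schedule, and higher with a secular trend.

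The lack of a calendar-period term is a real gap that affects both candidate analyses, so relabelling alone does not close it.

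**What to change.** 1. Replace the opening sentence on the primary analysis in Data analysis with, for example: *The primary analysis is the linear mixed model for the heiQ Skills and technique acquisition scale. The primary contrast is the experimental-minus-control difference at T1, using the T0 score and accounting for department (the randomised unit) and calendar period. The univariate comparisons are supportive.*
2. State whether T0 enters as a covariate or remains one of the repeated responses, so that the T1 contrast is unambiguous.
3. Name department explicitly, or confirm that organ and centre together identify it.
4. Restate the power in Sample size for the model with department and period, giving the assumed correlation, ICC and step schedule.

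Cost: items 1 to 3 are wording as far as the label, T0 and department are concerned. T0 is already collected, and department and inclusion date follow from the design. The period term is a change of model. Under the assumptions above it leaves about 27–42% power with 200 patients, so the restated figure would be well below 80%, and the sponsor should see it before settling the form of the time adjustment.

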**Fig. 1 Fig1:**
[figure not shown]
Flowchart of the study

In the month prior to the initiation of the experimental period for each department, the NPs will be trained in the delivery of the intervention. At this point in time, there will still be patients in the control period who are yet to complete the follow-up measure. During this month they may receive care in the form of a standard consultation from this NP. Therefore, there is potential for ‘contamination’ of these control period patients in the sense that their NPs will have already received the training associated with the intervention. To limit the risk of contamination, the following strategies will be put in place: standard care protocol will be used in all consultations for control period patients, and the questionnaires will not be administered by the NP but will be sent out by the researcher.

The ZENN intervention will be conducted in the outpatient clinic of each participating department. Due to the COVID-19 pandemic, the possibility of carrying out the intervention through tele-medicine is being examined. For the schematic overview of the inclusion, see Fig. 1. To enhance the validity of the study, the Standard Protocol Items: Recommendations for Interventional Trials (SPIRIT) guidelines [33] will be followed.

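### No stated between-group analysis adjusts for calendar time, so a secular trend would bias the unadjusted T1 test fully and the mixed model partly or not at all

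*Protocol article*

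**What the plan says.** The Study design and randomization section says that the trial "has an unblinded stepped wedge cluster randomized design" and that "Seven departments of five University Medical Centres will participate in the study". "All seven participating departments commence the study with standard care i.e. the control period", in September 2020. "The timing of transition of departments from control to experimental period is randomized", and "The first department will be randomized to commence the experimental period in March 2021". The two periods contain different patients. Trial status gives inclusion from September 2020 to an expected end in May 2022.

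The Data analysis section sets out these between-group analyses:

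- The analysis labelled primary is univariate: a t test or Mann-Whitney test at T1, and a 2 × 2 chi-squared test for the BAASIS.
- For the multivariable stage, "linear mixed models analysis will be conducted to account for repeated measures per patient, covariates organ and transplant centre and other significant covariates", using T0, T1 and T2.
- Medication adherence "will be analysed with a generalized estimating equations logistic regression".

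The Sample size section instead refers to the linear mixed model as the primary analysis. Whichever is meant, no calendar term is named. The Covariates section lists gender, age, education, organ and donor type for patients, but no inclusion date, step or period. The discussion of limitations does not mention secular trend.

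**The concern.** Only the switch date is randomised. Within a department, exposure is determined by enrolment date: before the switch is control, after it is experimental. Organ and centre terms remove level differences between departments but leave this before-after ordering untouched. After March 2021 some departments have switched while others have not. That overlap allows the intervention to be separated from time, but only if the model contains calendar time.

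Without such a term the estimate is largely a pooled before-after difference. Any change over the inclusion window in what patients report at T1 can be read as an effect of ZENN, in either direction. The article itself signals that conditions might not be constant: "Due to the COVID-19 pandemic, the possibility of carrying out the intervention through tele-medicine is being examined". At stake are the estimate and the error rate of the main comparison.

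**Working it through.** **The plan's own figure.** The Sample size section gives d = 0.38, 80% power, two-sided 0.05, ANCOVA with baseline and treatment group, 82 per group. With baseline correlation r, n = 2(1.96 + 0.8416)²(1 − r²)/d². At r = 0.5: 2 × 7.849 × 0.75/0.1444 = 81.5, so 82. The figure reproduces with r = 0.5, which the article does not state. The calculation has no department or period term.

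**Assumptions.** Only the start, the first switch (month 6) and the end of inclusion come from the article. Assumed: uniform accrual over 20 months, one department switching at each of months 6, 8, …, 18, ICC 0.05, r = 0.5, 200 patients, no true effect and a linear drift of 0.2 or 0.4 SD over the 20 months.

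**Calendar gap between groups.**

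- Within a department switching at month s: (s + 20)/2 − s/2 = 10 months, for any s.
- Pooled, without department: Σs = 84 and Σs² = 1120. Mean control enrolment = (1120/2)/84 = 6.67 months. Mean experimental enrolment = [(7 × 400 − 1120)/2]/(140 − 84) = 840/56 = 15 months. Gap = 8.33 months.

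**Bias = drift × gap/20.**

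- Unadjusted T1 test: 0.2 × 8.33/20 = 0.083 SD and 0.4 × 8.33/20 = 0.167 SD, whether or not T0 drifts.
- Department + baseline, T0 unaffected: 0.2 × 10/20 = 0.10 SD and 0.4 × 10/20 = 0.20 SD.
- Department + baseline, T0 drifting equally: multiply by (1 − 0.5), giving 0.05 and 0.10 SD.
- Change from T0, T0 drifting equally: the drift cancels and the bias is 0.

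The department-plus-baseline ANCOVA stands in here for the mixed model, whose contrast the article does not fix.

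**Simulation under these assumptions (drift 0.2 / 0.4 SD).**

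| Analysis | Does T0 drift? | Bias (SD) | Rejection |
|---|---|---|---|
| Unadjusted T1 test | either | about 0.08 / 0.16 | about 12% / 23% |
| Department + baseline | no | 0.10 / 0.20 | about 12% / 30% |
| Department + baseline | equally | about 0.05 / 0.10 | about 7% / 10% |
| Change from T0 | equally | about 0 | about 5% |
| Department + baseline + linear calendar time | either | about 0 | about 5% |

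With no drift at all the unadjusted test already rejects about 7% of the time because it ignores clustering; only the excess is due to trend.

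**Other schedules.** With 21 months of inclusion and the last switch at month 12, 15 or 18, the pooled gap is 0.75 to 0.84 years and the within-department gap 0.87 to 0.88 years. If the drift spares T0, a slope of 0.1 SD per year gives a bias of 0.07 to 0.09 SD, and 0.2 SD per year gives 0.15 to 0.18 SD (39 to 46% of 0.38).

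**Price of the adjustment.** In the simulated design the standard error rises from 0.136 to 0.215, a variance ratio of (0.215/0.136)² = 2.5. For d = 0.38, power moves from Φ(0.38/0.136 − 1.96) = Φ(0.83), about 80%, to Φ(0.38/0.215 − 1.96) = Φ(−0.19), about 42%. Across the other schedules the variance ratio is 2.7 to 3.4 with linear time and 2.9 to 5.2 with period categories. Power falls from 81–85% to 37–41% and 26–39% respectively.

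**The case against.** A reader might infer that any secular trend is counted in full as intervention effect, and that the 5% level is therefore lost. The documents do not support that. T0 is measured at each patient's own inclusion, so a smooth drift by enrolment date would normally move T0 too. The mixed model includes T0, and the plan also examines change from T0. If T0 and T1 drift equally and the contrast is taken against T0, the bias is nil. The full bias belongs to the unadjusted T1 test, and to any model if the trend affects T1 but not T0.

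The size is also hypothetical. The article reports no drift, gives only the first switch date and does not state uniform accrual. On COVID-19 it says only that remote delivery of the intervention and the training was being examined, so it does not establish that patients' outcomes were changing.

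Two further defences carry limited weight. The planned comparison of the two cohorts at T0 could reveal a drift, but it is a check and not an adjustment. A separate analysis plan might add a period term among the other significant covariates. However, entry there depends on significance, no calendar variable is listed, and the test labelled primary takes no covariates. The article fixes the tests and names the model terms, so this is more than a detail left for later.

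**Conclusion.** The point holds in this limited form: enrolment date and exposure are confounded within every department by design, and no stated between-group analysis breaks that link. The unadjusted T1 comparison is fully exposed to a trend. The mixed model is exposed partly or not at all, depending on two things the article leaves open: whether the trend shifts T0, and whether the contrast is against T0. The GEE names no calendar term either; its bias was not quantified.

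A drift of 0.4 SD over 20 months would bias the T1 test by about 0.16 SD, more than 40% of the assumed effect (0.16/0.38 = 42%), and raise rejection to about 23%. Half that drift gives about 0.08 SD and 12%. These figures illustrate the exposure; they rest on assumed drift, accrual, steps, ICC and correlation. What does not depend on them is that the randomised switch dates protect the comparison against secular trends only if calendar time is in the model. This should be corrected before analysis.

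**What to change.** Name one primary model for the heiQ Skills and technique acquisition scale at T1, with treatment, baseline score, department as a fixed effect and calendar time of enrolment. Enter calendar time as the periods between successive switch dates, or as a linear or spline term in enrolment month if periods are sparse. Include it regardless of significance. Use the same calendar and department terms in the T2 comparison, the secondary-outcome models and the BAASIS model. Drop the unadjusted tests as primary and, at most, report them as descriptive.

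Inclusion dates should be available, because T1 and T2 fall six and twelve months after inclusion, but the article does not list them; state that they are recorded.

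The change is more than wording. Variance rises about 2.5 times or more under the assumptions above, and the 80% power for 82 per group (100 after allowances) was calculated without period or department. Restate power for the period-adjusted model with the actual step schedule, and either revise the sample size or declare the reduced power.
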